### Treatment visits

The women will be instructed to engage in intercourse once every 2 or 3 days. A serum progesterone measurement will be taken in the local laboratory on day 21 of the menstruation cycle. An elevated progesterone level > 3 ng/ml will be considered to indicate evidence of ovulation. If there is no ovulation, the serum progesterone level will be checked every week until ovulation. If ovulation occurs, a serum pregnancy test will be performed 1 week later. For the duration of the treatment, urine LH or human chorionic gonadotropin (HCG) levels can be measured, depending on the judgment of the PI, in order to obtain timely information on ovulation or pregnancy and thus to instruct the participant to continue engaging in intercourse or to stop the intervention. We will determine whether the women have an ovulation response based on the serum progesterone level, and there will be three possible scenarios—ovulation, delayed ovulation, or no ovulation—as follows:
*Ovulation*: Serum progesterone level on day 21 of the cycle > 3 ng/ml. A serum pregnancy test will be performed 1 week later to exclude pregnancy. In the letrozole and placebo letrozole groups, letrozole or placebo letrozole will be started between days 3 and 7 of the new cycle, and the letrozole or placebo letrozole dose will be maintained at the same level as the previous cycle.*Delayed ovulation*: Serum progesterone level on day 21 of the cycle < 3 ng/ml. In this case, we will wait 1 week and then check the serum progesterone level again. If the second measurement shows that ovulation occurred (serum progesterone > 3 ng/ml), a serum pregnancy test will be performed 1 week later to exclude pregnancy. In the letrozole and placebo letrozole groups, letrozole or placebo letrozole will be started between days 3 and 7 of the new cycle, and the letrozole or placebo letrozole dose will be maintained.*No ovulation*: Negative serum progesterone on day 21 and day 28. In the letrozole and placebo letrozole groups, women will take letrozole or placebo letrozole on day 28 of the cycle, and then one more tablet per day will be given for 5 consecutive days until the maximum daily dose of three tablets per day. Day 28 will be defined as day 1 of the next cycle, and a serum progesterone measurement will be made every week until ovulation.

Every menstruation will be recorded, including the date, amount, and duration of menstruation.

### End-of-treatment visit

The end-of-treatment visit will be performed when the women conceive or finish four cycles of treatment. Baseline measures will be repeated in all subjects, including vital signs, height, weight, hip, and waist measurements; hirsutism and acne assessments; sex hormone steroids (FSH, LH, and total T for women who are not pregnant and β-HCG, P, E2, and total T for women who are pregnant); SHBG; metabolic profile (glucose and insulin concentrations, HbA1C, C-peptide, cholesterol, triglycerides, HDL-C, and LDL-C); liver profile (AST, ALT, and total bilirubin); and renal profile (BUN and creatinine). Subjects will return menstrual and intercourse journal logs, and their AEs and concomitant medications will be recorded. Fasting blood samples will be obtained, and TCM syndrome diagnosis and the SF-36, PCOS-QOL, ChQOL, PSQI, Zung SAS, and Zung SDS questionnaires will be repeated.

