**Methods/design:**

The study is designed as an assessor-blinded RCT. A total of 1100 infertile women with PCOS will be recruited from 28 hospitals and randomly allocated to 4 groups: personalized acupuncture, fixed acupuncture, letrozole, or placebo letrozole. They will receive treatment for 16 weeks, and the primary outcome is live birth. Secondary outcomes include ovulation rate, conception rate, pregnancy rate, pregnancy loss rate, changes in hormonal and metabolic parameters, and changes in quality of life scores. Adverse events will be recorded throughout the trial. All statistical analyses will be performed using IBM SPSS Statistics version 21.0 software (IBM Corp., Armonk, NY, USA), and a *P* value < 0.05 will be considered statistically significant.

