### Recruitment

A total of 1100 infertile women with PCOS will be recruited from 28 hospitals in China and will be randomly allocated to the following four groups: personalized acupuncture, fixed acupuncture, letrozole, or placebo letrozole. The women will be recruited through advertisements in local newspapers and bulletin boards in each trial center. Prior to participation, eligible women will sign the consent form after a detailed explanation of the study design and comprehensive counseling.

Inclusion criteria are as follows:
Age between 20 and 40 yearsChronic oligomenorrhea or amenorrhea. *Oligomenorrhea* is defined as an intermenstrual interval > 35 days or < 8 menstrual bleedings in the past year. Amenorrhea is defined as an intermenstrual interval > 90 days.Hyperandrogenism (either hirsutism or hyperandrogenemia) or polycystic ovaries on ultrasound. Hirsutism is determined by a modified Ferriman-Gallwey (FG) score ≥ 5 at screening examination [23], and biochemical hyperandrogenism is defined as total testosterone (T) > 2.6 nmol/L and free T ≥ 6.0 pg/ml [24]. (The cutoff level might differ for each study site.) Polycystic ovaries are considered present when the number of small antral follicles (2–9 mm in diameter) is ≥ 12 or the ovarian volume is > 10 ml on transvaginal ultrasound [25].At least one patent tube shown by hysterosalpingogram, contrast sonography, or diagnostic laparoscopy within 3 years if the patient does not have a history of abortion or pelvic operation. If the patient has a history of pregnancy and no history of pelvic operation within the past 5 years, she will not be required to undergo a tubal patency test.Sperm concentration ≥ 15 × 10^6^/ml and total motility ≥ 40% or a total motile sperm count ≥ 9 million in the semen analysis of the husband [26].The couple agrees to have regular intercourse (i.e., two or three times per week) during the study period.

Exclusion criteria are as follows:
Other endocrine disorders:

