
### Intervention

All participants will be informed of the benefits of regular physical exercise and will be instructed to have regular intercourse every 2 to 3 days. Women in both the personalized and fixed acupuncture groups will receive acupuncture treatment three times per week with a maximum of 48 treatment sessions over 16 weeks. Acupuncture treatment will be started between days 3 and 7 of the spontaneous menstrual cycle or between days 3 and 7 after withdrawal bleeding following progestin. They will be contacted by phone if they miss the scheduled appointment. If they miss appointments during treatment, missed appointments will be clearly documented in the record for later analysis. They will be treated for up to 16 weeks. If they become pregnant, the treatment they are receiving will be stopped. For the personalized and fixed acupuncture groups, credibility and expectancy questionnaires will be completed at the third acupuncture treatment and at the last acupuncture treatment.

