### Blinding

The acupuncture groups will be known only to the acupuncturists and the ResMan data manager. The letrozole and the placebo letrozole pills with the same appearance will be organized in a kit consisting of one cycle of pills for each participant, and one participant will at most take 45 pills over a total of 4 cycles. The sealed envelope with four cycles’ worth of pills will be labeled with an identification number mapped to the letrozole or placebo letrozole allocations, which will be known only to the ResMan staff. Participants and investigators will be blinded to the letrozole or placebo letrozole allocation. All outcome assessors and the statisticians performing the data analysis will be blinded to group allocation. Except for emergencies, unblinding of individual participants will not take place until all pregnant participants giving birth and the outcomes of the births have been reported to the DCC. In the event that emergency unblinding is needed, only the site principal investigators (PIs) will be able to unblind the participant to treatment by contacting the director of the DCC. The site PIs and DCC staff will receive notification from the central randomization service when emergency unblinding has occurred.

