### Outcomes

#### Primary outcome

The primary outcome is the live birth rate, defined as delivery of any viable infant after 28 weeks of gestation.

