#### Conception rate

Conception will be defined as a positive serum β-HCG measurement. Thus, the cumulative conception rate will be the proportion of women who conceive during the four treatment cycles among all women in the primary analysis.

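### Treatment and follow-up for conception end by two unreconciled clocks (16 weeks and four cycles), and live birth has no conception window, so time at risk can differ between acupuncture and pill arms

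*Protocol article*

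**What the plan says.** **Calendar clock.** The abstract says of all four groups: "They will receive treatment for 16 weeks, and the primary outcome is live birth". Table 3 heads the treatment visits of all four arms with 16 weeks. The Intervention section schedules acupuncture "three times per week with a maximum of 48 treatment sessions over 16 weeks" and adds: "They will be treated for up to 16 weeks".

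**Cycle clock.** The End-of-treatment visit section states: "The end-of-treatment visit will be performed when the women conceive or finish four cycles of treatment". Under Blinding, the pill supply is such that "one participant will at most take 45 pills over a total of 4 cycles". The conception rate is "the proportion of women who conceive during the four treatment cycles", with all women in the primary analysis as denominator.

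**Cycle length.** In the Letrozole and Treatment visits sections, a pill-arm woman who does not ovulate starts a new cycle at day 28. After ovulation or delayed ovulation, the next course waits for days 3 to 7 of the new cycle. At entry, oligomenorrhea "is defined as an intermenstrual interval > 35 days" or by fewer than eight bleeds in the past year.

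**Primary outcome and test.** Live birth is "defined as delivery of any viable infant after 28 weeks of gestation". No limit is set on the date of conception. Follow-up of pregnancies covers positive tests in the course of the study but does not say when that ends for a woman who has not conceived. Data analysis specifies a Pearson chi-square test as the primary analysis.

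**The concern.** Live birth is compared as a simple proportion, which is fair between arms only if women in each arm have the same time in which a conception can count. The protocol fixes that time in weeks in one place and in cycles in another. In a population enrolled for long or absent cycles, the two are not interchangeable.

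The first and third hypotheses under Objectives (letrozole versus personalized acupuncture, fixed acupuncture versus placebo letrozole) each set an acupuncture arm against a pill arm. If the clocks work differently in the two kinds of arm, part of an observed difference, or part of a missing one, could come from unequal exposure and not from treatment. The time-to-pregnancy analysis does take time into account, but it is secondary and does not correct the primary test.

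**Working it through.** **1. The plan's own figures.**
- Pill maximum: one, two, three and three pills per day for 5 days gives 5 × (1 + 2 + 3 + 3) = 45. This matches Blinding and confirms that the pill supply is planned by four cycles.
- Sample size, 25% versus 15%, two-sided 0.05, 80% power, pooled variance: n = [1.960 × √(2 × 0.20 × 0.80) + 0.842 × √(0.25 × 0.75 + 0.15 × 0.85)]² / 0.10² = 250 per arm, as stated. The figure of 250 is used in step 4.

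**2. When the two clocks agree.** 16 weeks = 112 days, and four cycles of L days take 4L days. They are equal only at L = 28.

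| Cycle length L (assumed) | Four cycles | Excess over 16 weeks | Cycles in 112 days |
|---|---|---|---|
| 28 days | 16.0 weeks | 0 | 4.0 |
| 30 days | 17.1 weeks | 1.1 | 3.7 |
| 32 days | 18.3 weeks | 2.3 | 3.5 |
| 35 days | 20.0 weeks | 4.0 | 3.2 |
| 42 days | 24.0 weeks | 8.0 | 2.7 |

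The document gives no on-treatment cycle length, so L is an assumption throughout.

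**3. Where the protocol fixes L at 28.** It does so only for pill-arm women without ovulation, who finish four such cycles in exactly 112 days. In delayed ovulation, progesterone is positive at about day 28 and the pregnancy test follows a week later, at about day 35. That cycle exceeds 28 days on the protocol's own schedule. No rule resets the cycle in the acupuncture arms. A woman there whose cycles stay above 35 days completes fewer than 112/35 = 3.2 of them in 16 weeks, so for her the 16-week cap and the four-cycle visit rule cannot both be met.

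**4. What unequal exposure could do.** Assume two arms with the same true 16-week rate p and a constant hazard, with every woman in one arm observed for w weeks and every woman in the other for 16. The rate over w weeks is 1 − (1 − p)^(w/16). For w = 20 (35-day cycles) the exponent is 140/112 = 1.25. The last column is the chance that the chi-square test at nominal 5%, with 250 per arm, declares a difference.

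| 16-week rate p | Rate over 20 weeks | Gap (points) | Rejection probability |
|---|---|---|---|
| 5% | 6.2% | 1.2 | 9% |
| 15% | 18.4% | 3.4 | 17% |
| 25% | 30.2% | 5.2 | 26% |
| 35% | 41.6% | 6.6 | 33% |

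For p = 25%: 1 − 0.75^1.25 = 0.302. Over other windows the same 25% becomes 27.6% at 18 weeks (gap 2.6) and 35.0% at 24 weeks (gap 10.0). The target difference in Sample size calculations is 10 points.

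**The case against.** The strongest reply is that both clocks are written for every arm. The abstract and Table 3 give 16 weeks to all four groups, and the End-of-treatment visit and Conception rate sections give four cycles to all women. No sentence says that acupuncture stops by the calendar while pills continue past week 16. This stands. The arm-specific split is an inference from the 48-session cap on one side and the four-cycle pill supply on the other. What the text shows is an unreconciled contradiction.

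A reader might infer that the pill arms generally have the longer exposure, so that letrozole is favoured. The documents do not support that:
- Pill-arm women who never ovulate finish in exactly 16 weeks. The 45-pill maximum is itself reached only after no ovulation in cycles 1 and 2, both of which then last 28 days.
- If four cycles governed everyone, acupuncture women with long natural cycles could be observed longer than those pill-arm women, which reverses the direction.
- With no conception window at all, late conceptions in acupuncture women are not excluded either. The contrast of 112 with 140 days is one possible way of carrying out the text, not a rule that it states.

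The 35-day interval is an entry criterion and says nothing certain about cycles on treatment. At the 5% assumed for placebo letrozole the illustrated shift is only 1.2 points.

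It can also be said that a condensed article may leave the conception cut-off to the full protocol or SAP. A missing cut-off alone would not be a point. Here, however, the article prints two conflicting end rules, one of which also defines a secondary outcome.

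**Conclusion.** The point holds as a possible bias arising from conflicting text. Treatment and follow-up for conception end at 16 weeks or after four cycles, and the two coincide only with 28-day cycles. The primary outcome has no window that would make the difference harmless, and the primary test does not adjust for exposure. Time at risk can therefore differ between acupuncture and pill arms; the document does not allow its direction or size to be determined.

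The figures of 5.2 points at a 25% rate and 1.2 points at a 5% rate are upper-end illustrations. They rest on a constant hazard, on 35-day cycles, and on every woman in one arm and none in the other having the longer window. A mixture of cycle lengths, or one clock applied in all arms, would give less. The point has no bearing on the stated sample size. It should be settled before the outcome data are unblinded.

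**What to change.** Define the primary outcome as live birth resulting from a conception dated within one fixed window from randomization, with the same length in all four arms, and state how conception is dated. Use the same window for conception rate, pregnancy rate and time to pregnancy. Report live births from conceptions outside it as a sensitivity analysis.

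Separately, the investigators must reconcile the 16-week statements (abstract, Intervention, Table 3) with the four-cycle statements (Blinding, End-of-treatment visit, Conception rate) on treatment length and on the timing of the end-of-treatment visit. No choice between them is proposed here.

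The cost is mainly wording, and the number of women does not change. Serum pregnancy tests are already scheduled. If the window outlasts some women's last visit, pregnancy status at its close has to be obtained in the same way in every arm. There are two small downsides. Some later conceptions leave the primary count. The 35% assumed for letrozole is stated for four cycles, so it should be checked against whatever window is chosen.

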### Pregnancy visit (only with conception)

Serum progesterone and β-HCG levels will be determined at local sites to document ovulation and pregnancy. A serum β-HCG > 10 IU/L will indicate pregnancy, and in pregnant women, the serum β-HCG level will continue to be checked on a weekly basis. Pelvic ultrasound will be performed to determine the location and number of fetuses when the serum β-HCG is 2000–4000 IU/L. Pelvic ultrasound will then be performed every 2 weeks until viability of the pregnancy is determined by visualization of fetal heart motion.

Women who conceive will be referred to their prior or referring doctors for antenatal care at around 10–12 weeks of gestational age. Subsequent arrangements will be performed at weeks 18–24, 32, and 36 or upon the prescription of the obstetrician. In the present trial, pregnant women who present with threatened miscarriage or who are considered to have a significant risk for miscarriage can be given oral Duphaston (10 mg three times per day; Solvay Pharmaceuticals B.V., Veenendaal, the Netherlands) until 12 weeks of gestation or until 1 week after the vaginal bleeding stops. This information will be documented in the study records. No other medications, including HCG, herbal medications, or acupuncture, will be given.

### Follow-up of pregnancies

Women who conceive will be referred to their prior or referring doctors for antenatal care at around 10–12 weeks of gestational age, and they will be seen in follow-up until delivery or termination of gestation. All pregnancies (including multiples) will be followed to monitor weight, glucose tolerance, blood pressure, and fetal growth and to determine the pregnancy outcomes. Glucose tolerance will be measured by oral glucose tolerance test in all pregnant women at 24–28 weeks of pregnancy. Women will be instructed to inform the study personnel of the outcomes of the pregnancy, and we will obtain delivery records from the obstetricians to determine the birth weight, length of gestation, and any prenatal complications in the mother or neonatal complications in the infant. Phone contacts will be initiated if the pregnant woman has not contacted the study personnel within 6 weeks of the original estimated date of childbirth.

We will collect pregnancy outcome data and track the outcomes of all women who have a positive serum pregnancy screen during the course of this study. We will record biochemical pregnancies (defined as positive serum pregnancy screens without ultrasonically detected pregnancies), ectopic pregnancies, and all intrauterine pregnancy losses both before and after 20 weeks, including miscarriages, abortions, fetal deaths, and stillbirths.

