### Study-specific visits and procedures

Women will attend up to five different clinic visits, including the screening visit, the baseline visit, the treatment visits, the pregnancy visit, and the end-of-treatment visit (Fig. 2, Table 3). Adverse events (AEs) and concomitant medications will be recorded at every visit. Face-to-face adherence reminders will be given at each study visit.

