**Fig. 2 Fig2:**
[figure not shown]
Study flowchart

**Table 3 Tab3:** Overview of the study visits

	Screening visit	Baseline visit	Treatment visits (16 weeks)				End-of-treatment visit	Pregnancy visit
			Personalized acupuncture	Fixed acupuncture	Letrozole	Placebo letrozole		
Sign consent	×							
History	×						×	
Urine pregnancy test	×	×	×	×	×	×		
Physical examination	×						×	
Transvaginal ultrasound	×							×
Semen analysis	×							
Tubal patency test	×							
HPV or TCT	×							
Preconception counseling	×							
Fasting blood for laboratory tests	×						×	
Blood sample collection		×					×	
Serum progesterone assay	×		×	×	×	×		×
Serum HCG assay	×	×	×	×	×	×		×
Questionnaires		×					×	
Acupuncture treatment (three times weekly)			×	×				
Assess adverse events and concomitant medications			×	×	×	×	×	×
Pregnancy and neonatal records								×

Physical examination: weight, height, waist circumference, hip circumference, Ferriman-Gallwey/acne

Fasting blood for laboratory test: follicle-stimulating hormone, luteinizing hormone, sex hormone–binding globulin, total testosterone, free testosterone, estradiol, prolactin, fasting blood glucose, fasting insulin, C-peptide, glycated hemoglobin, cholesterol, triglycerides, high-density lipoprotein cholesterol, low-density lipoprotein cholesterol, complete blood count, thyroid profile, renal profile, and liver profile

Transvaginal ultrasound: endometrial thickness, ovarian volume, antral follicle count, and size of ovarian cysts or developing follicles

Preconception counseling: TORCH (toxoplasmosis, rubella, cytomegalovirus, and herpesvirus) and human immunodeficiency virus screening

Blood sample collection: serum for the central core laboratory

*Abbreviations: HCG* Human chorionic gonadotropin, *HPV* Human papillomavirus, *TCT* ThinPrep cytologic test

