#### Adverse events

All AEs will be categorized, and the percentage of patients experiencing AEs and serious adverse events (SAEs) during the treatment period and follow-up period will be documented and reported. For fetuses, SAEs and AEs will be reported as those occurring after 20 weeks of gestation through birth, and for newborns, SAEs and AEs will be reported as those occurring within 28 days after birth. SAEs will include events that are fatal or immediately life-threatening, severely or permanently disabling, or that require hospitalization; overdoses (intentional or accidental); congenital anomalies; pregnancy loss after 12 weeks of gestation; neonatal death up to 6 weeks after delivery; or any event deemed to be serious by the site PIs. The Data and Safety Monitoring Board (DSMB) will review AEs on a quarterly basis and will review SAEs immediately.

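### Newborn events are to be reported for 28 days (deaths for 6 weeks), but stated follow-up ends at delivery and only women who have not reported are phoned

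*Protocol article*

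**What the plan says.** Two sections of the protocol article bear on this.

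**What is to be reported.** Under Adverse events, "for newborns, SAEs and AEs will be reported as those occurring within 28 days after birth". The list of serious events in the same section includes congenital anomalies and "neonatal death up to 6 weeks after delivery". The monitoring board is to review serious events immediately.

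**How the information is to be obtained.** Under Follow-up of pregnancies, women are referred out for antenatal care and "they will be seen in follow-up until delivery or termination of gestation". The outcome then reaches the study by two routes:
- "Women will be instructed to inform the study personnel of the outcomes of the pregnancy";
- the study collects the obstetricians' delivery records, which are to show complications of the infant as well as of the mother.

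A study-initiated call is the backstop: "Phone contacts will be initiated if the pregnant woman has not contacted the study personnel within 6 weeks of the original estimated date of childbirth".

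Study-specific visits and procedures lists the visit types as "the screening visit, the baseline visit, the treatment visits, the pregnancy visit, and the end-of-treatment visit". Table 3 marks the row "Pregnancy and neonatal records" under the pregnancy visit and has no postpartum column.

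**The concern.** The reporting commitment runs past the point at which stated follow-up stops. The one call that could bridge the gap goes only to women who have not been in touch. A site that follows the text has no instruction to ask a mother who phoned in her delivery whether the infant later died, was admitted or was found to have an anomaly.

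Two things are at stake. The first is completeness: a low newborn event count could partly mean that nobody asked. The second is evenness: whether a late event is sought depends on how the mother behaved, because silence triggers a look-back and prompt reporting does not. Prompt review of serious events by the monitoring board also depends on the study learning of them.

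**Working it through.** The plan gives no figure on this point to reproduce. The check is to set the time windows side by side.

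**Inputs**
- Newborn adverse event window: 28 days after birth (Adverse events).
- Neonatal death window: 6 weeks = 42 days after delivery (Adverse events).
- Call trigger: no contact by 6 weeks from the original due date (Follow-up of pregnancies), read as 6 weeks after it.
- Assumption: the due date is 40 completed weeks, so the call falls at 40 + 6 = 46 weeks.
- Recruitment ends 13 August 2021 and trial procedures end by the end of May 2022 (Trial status).
- Live birth rates of 35%, 25%, 15% and 5%; 275 enrolled or 250 required per group (Sample size calculations); 28 hospitals (Recruitment).

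**Step 1. When the call reaches a woman who has not reported.** Days after birth = (46 − gestational week at birth) × 7.

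| Birth at week | Call, days after birth | Relative to day 28 | Relative to day 42 |
|---|---|---|---|
| 28 | 126 | 98 later | 84 later |
| 37 | 63 | 35 later | 21 later |
| 40 | 42 | 14 later | same day |
| 41 | 35 | 7 later | 7 earlier |
| 42 | 28 | same day | 14 earlier |

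For births at 28 to 42 weeks the call never comes before the 28-day window ends, so it can cover that window by recall. For births after 40 weeks it can come before the 6-week death window closes.

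**Step 2. A woman who reports at or soon after delivery.** The condition for the call is not met. No visit type is postpartum and no other study contact after delivery is stated. What remains is whatever the delivery records contain. Events noted there are captured; events after those records close have no stated route.

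**Step 3. The calendar.** 13 August 2021 + 40 weeks = 20 May 2022. Adding 28 days gives 17 June 2022; adding 6 weeks gives 1 July 2022. Both fall after the end of May 2022, with nothing yet allowed for the 16 treatment weeks. For the last women recruited, the stated end date leaves no room for either newborn window.

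**Step 4. How many births are concerned.** Sum of the assumed rates = 0.35 + 0.25 + 0.15 + 0.05 = 0.80.
- All enrolled: 275 × 0.80 = 220 births; 220 / 28 = 7.9 per site.
- Required number only: 250 × 0.80 = 200 births; 200 / 28 = 7.1 per site.

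These are births at which the question arises, not missed events.

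**The case against.** The strongest reply is that this infers from silence. The call is written as a backstop, and nothing says that it is the only contact after birth. The document is a journal article, and call scripts, the timing of record requests and neonatal case report pages would normally sit in the full protocol. Delivery records do cover neonatal complications, Table 3 has a row for neonatal records, and no retrieval date is given, so the records may reach some way past birth. Women who have not reported do get a call.

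Much of this stands, and it limits the point. It is not true that no contact can observe the newborn period: delivery records and late calls each capture part of it. But the article does more than omit detail. It states an end of follow-up and a condition for the call, and these do not match the reporting window that it also states.

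Three stronger readings are tempting and are not supported:
- **Newborn events will be missed in most births.** The documents give no event rate, no usual reporting day and no date at which records close. Most births need have no late event.
- **Pregnancy losses after hand-over go unsought until the call after the due date.** Pregnancy visit schedules arrangements at weeks 18–24, 32 and 36, with the obstetrician's prescription as an alternative. Follow-up of pregnancies adds a glucose tolerance test at 24–28 weeks in all pregnant women and tracking of every positive pregnancy test. A loss could surface at any of these.
- **The comparison between arms is biased.** The contact rule is the same in all four groups, and nothing shows that reporting behaviour differs between them.

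**Conclusion.** The mismatch is real and lies in the stated text. For women who report delivery promptly, newborn events after the delivery records close have no stated way into the study, while women who do not report get a retrospective call. Newborn safety data may be incomplete and unevenly ascertained. This rests on following the follow-up section as written; the timings in the table also assume a 40-week due date.

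The size of the loss cannot be computed from the documents. About 200 to 220 births fall under the rule at the plan's own live birth rates. Live birth is known at delivery, so the primary analysis is not touched. The point is worth correcting because the trial has undertaken to report these events and the remedy is cheap.

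**What to change.** - Make the existing phone call unconditional: one short scripted call to every woman who delivers, timed from the actual delivery and made after the longer newborn window in the Adverse events section has closed. Ask about infant death, hospital admission and anomaly, and record the infant's vital status.
- In Follow-up of pregnancies, extend the end of follow-up from delivery to the end of that window.
- Reconcile the 28-day and 6-week windows, or state that they serve different purposes.
- Move the end-of-procedures date in Trial status if the last births and their newborn window need it.

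Cost: a small amendment and about 200 to 220 calls in all, roughly 7 to 8 per site across 28 sites. Some of these would be made anyway to women who had not reported. One limit remains: a single call after the window closes makes ascertainment more complete and more even, but the study may still learn of an event weeks after it happened, so the monitoring board's review can be immediate only from the time of notification.
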